### Randomization and blinding

After baseline assessments (T0), participants will be divided into two groups (one experimental group with trampoline training [EG] and one control group [CG]). Online software will be used to generate the randomization plan using a random block sizes method. This randomization procedure assures an allocation concealment format—i.e., the individual in charge of this task does not know what the next group allocation will be. This researcher will assign participants to their groups and perform follow-up measurements (Fig. 1). The data analysts will be blind to the group control or intervention.

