### Data collection

Assessments will take place at APDPk by a blinded researcher in the week before (T0), after 8 weeks of training protocol (T1), and 3 months after the end of the program (T2). The same protocol will be applied, composed of scales/questionnaires and validated assessment instruments, referenced below. The researchers who will perform these assessments will not participate in the intervention. All participants will be assessed in the ON medication phase with the following specific clinical scales and tests that will have their order randomized. Patients will be assessed for (a) balance (Mini-BEST Test) [12], (b) gait (Motor and Cognitive Timed Up Go (TUG)) [12], (c) clinical impairments (Movement Disorder Society Unified Parkinson Disease Rating Scale (MDS-UPDRS)) [31], (d) frequency and severity of falls (falls weekly registry) [12], (e) fear of falling (Falls Efficacy Scale (FES-I)) [32], (f) physical capacity (6-min walking distance test (6MWD)) [12], (g) cognition (Montreal Cognitive Assessment (MoCA)) [33], and (h) quality of life (PDQ-8) [34, 35]. Additional gait and balance assessments will be conducted using accelerometers placed on the ankles and standing on a force plate. Participants will be asked to walk on a treadmill for 10 min at their preferred walking speed. Moreover, their balance will be tested in both eyes opened and closed conditions. They will be asked to remain still for 2 min. Researchers that will conduct the assessments will be trained by a senior and experienced researcher. The database obtained will undergo a double check (two different researchers) to identify potential failures/errors.

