The informed consent form will contain comprehensive information about contents, objectives, duration, procedures, voluntariness, and possible risks of study participation. It will be emphasized that the participant is at liberty to withdraw their consent to participate at any time without penalty or loss of benefits to which the participant is otherwise entitled. Participants who refuse to give or withdraw written informed consent will not be included or continued in this study, but this will not impact their subsequent care. During the screening visit, the participants will be given an explanation of the objective and compliance needed for the study. Any questions will be considered and answered. In case of an agreement to voluntarily participate in the study, the participant must sign two copies of the informed consent form; one will be given to the participant, and the other form will be retained at the local study center. The consent forms will be kept separately from the data. Essential documents will be archived in a way that ensures that they are readily available, upon request, to the competent authorities. Case report forms (CRFs) will be used as source documents for collecting data. These CRFs will be encoded (a coded combination of numbers and letters, e.g., LIFTT 01), so that it is impossible to assign the data contained in a CRF to an individual participant. Only the project coordinator will have access to the decoder grid. All paper copies will be stored in a locked file, as well as all electronic data. Data will be maintained for 5 years in a restricted access locked file cabinet at Egas Moniz - Cooperativa de Ensino Superior, C.R.L. After that, they will be destroyed. All data will be confidentially locked, and all subject information will remain anonymous.

Participants who are unable to continue to participate in the intervention will withdraw from the intervention. On withdrawal, we will register the date and reason for withdrawal.

They will also continue to be followed up and data collected until the end of the study unless they explicitly withdraw their consent.

Regarding drafting, editing, accountability of the data, and study authorship, we will follow the current version of the International Committee of International Journals Editors (ICMJE) recommendations. The data obtained will only be used in the context of this study and professional writers will not be hired for this study.

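### The protocol has the researcher who allocates participants also take the follow-up measurements, yet promises blinded assessment; the two sections contradict each other and must be reconciled

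*Protocol article*

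**What the plan says.** Randomization follows the baseline visit: "After baseline assessments (T0), participants will be divided into two groups". The Randomization and blinding section describes concealment by saying that "the individual in charge of this task does not know what the next group allocation will be", and goes on: "This researcher will assign participants to their groups and perform follow-up measurements". The only blinding named in that section is that of the analysts: "The data analysts will be blind to the group control or intervention".

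The Data collection section says "Assessments will take place at APDPk by a blinded researcher" and lists T0, T1 and T2 as the occasions. It adds: "The researchers who will perform these assessments will not participate in the intervention".

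The abstract gives the primary outcomes as balance (Mini-BEST Test and nonlinear analysis) and gait (Motor and Cognitive Timed Up and Go, TUG, and nonlinear analysis). The control group has usual care and the assessments, with no sham or alternative training.

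**The concern.** One section gives a single person two jobs, allocating participants and measuring them at follow-up. The other says that whoever measures them is blinded. A reader cannot tell which rule the trial follows.

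Participants know whether they trained on a trampoline, so a blinded assessor is the main safeguard for outcomes that an examiner administers. T0 is measured before allocation exists. Any influence of knowing the arm would therefore enter only after baseline, and the planned treatment-by-time analysis looks for benefit in exactly that change. Blinding the analysts does not help, because the scores they receive would already carry the influence.

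**Working it through.** No figure in the protocol bears on this point, so the check is first a comparison of text and then an illustration.

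**Comparison of the two sections**

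1. *Who is meant.* The researcher who assigns and measures is the individual just described as being in charge of the randomization task.
2. *What that person knows.* The concealment described covers the next allocation, which has not yet been made. It does not hide allocations already made. By the time of any follow-up visit, the assigner knows the arm.
3. *What the other section requires.* Data collection promises blinding at T0, T1 and T2.
4. *Whether other text resolves it.* Data collection keeps assessors out of the intervention but says nothing about keeping them out of allocation. Analyst blinding concerns a later step. Fig. 1, cited at the sentence in question, is not available here, but no figure could make both sentences true as written.
5. *Which visits are exposed.* T0 is not, because it precedes randomization. T2 is: the abstract, the Design section and the Interventions section all use the term follow-up for the 3-month period after training. T1 is probably exposed, since follow-up measurements can also mean every measurement after baseline, but the text does not settle this.
6. *Which outcomes are exposed.* The Mini-BEST Test is a scored test given by the assessor, so it leaves most room for judgement. The TUG is administered but timed, and leaves less. The accelerometer and force-plate measures leave least. This ordering is a judgement; the article does not describe scoring procedures.

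**Illustration of size**

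Inputs: 26 per group (required) and 30 per group (recruited), with two-sided alpha of 5%, from Sample size calculation. The bias *b*, in SD units and favouring the trained arm, is assumed because the documents give none.

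With no true effect, the two-sample t statistic with *n* per group follows a noncentral t distribution with 2*n* − 2 degrees of freedom and noncentrality λ = *b*·√(*n*/2). The rejection rate is P(|T| > t₀.₉₇₅).

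- *n* = 26: √13 = 3.606, 50 degrees of freedom.
- *n* = 30: √15 = 3.873, 58 degrees of freedom.

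| Assumed shift *b* (SD) | λ, 26 per group | Rejection rate | λ, 30 per group | Rejection rate |
|---|---|---|---|---|
| 0 | 0 | 5.0% | 0 | 5.0% |
| 0.1 | 0.361 | 6.4% | 0.387 | 6.7% |
| 0.2 | 0.721 | 10.9% | 0.775 | 11.9% |
| 0.3 | 1.082 | 18.6% | 1.162 | 20.8% |

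These rates are for a simple t-test at one time point, the test behind the sample size. The planned analysis is a two-way repeated-measures ANOVA, for which the rates would differ.

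**The case against.** The strongest reply is that Data collection is the section dedicated to this matter. It states blinding explicitly, speaks of several assessors and separates them from treatment, so the sentence under Randomization and blinding may be a drafting slip. That may well be so. It limits the claim to a contradiction in the text, with a consequence that depends on which sentence is followed. It does not remove the need for correction, because as written one section permits what the other rules out.

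Four stronger readings are tempting and are not supported:

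- *That T1 and T2 are both certainly unblinded.* The article mostly uses follow-up for the 3-month phase, so T2 follows from the text and T1 is only probable.
- *That all primary outcomes are compromised.* The nonlinear balance and gait analyses are also primary, and the instrumented recordings from accelerometers and a force plate are little exposed to a rater.
- *That the bias can be stated as a share of the design effect.* The 0.7 in the sample size section is given as an example for the FES-I, a secondary fear-of-falling scale. No design effect is given for the Mini-BEST Test or TUG, so such a ratio would mean little.
- *That the project coordinator holds the allocation list and is the natural allocator.* The statement "Only the project coordinator will have access to the decoder grid" concerns the key linking coded case report forms to individuals. Nothing there speaks of allocation, or of whether the coordinator assesses outcomes.

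It is also fair to say that the direction of any bias is not established by the documents. The illustration assumes that it favours the trained arm. The Discussion does state that an increase in the Mini-BEST score is expected, which makes that direction plausible but no more.

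**Conclusion.** The contradiction is real, and confidence in it is high. Under the randomization section as written, the assessor at T2, and probably at T1, knows the arm, contrary to the Data collection section. The documents do not show that assessment has in fact been unblinded, nor that the results are biased.

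If the randomization sentence is the rule followed, observer bias could enter chiefly through the Mini-BEST Test and to a lesser degree through the TUG. Its size is unknown. The illustration shows that even an assumed shift of 0.2 SD would roughly double the nominal 5% error rate at either group size. It rests on an assumed shift, an assumed direction and a t-test, and the finding does not depend on it. Because the error touches the main safeguard in a trial with unblinded participants and a usual-care control, it should be corrected.

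**What to change.** Amend Randomization and blinding so that allocation is released by a team member who takes no part in outcome assessment. State there, in line with Data collection, that T1 and T2 are measured only by assessors who have no access to the allocation.

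The Trial status section says that recruitment is still under way, so the change can protect visits still to come. If the allocator has already measured any follow-up visits, record and report which ones. Run a sensitivity analysis without them where enough blinded visits remain. If one person measured everyone, that analysis would leave no data for those visits, and the assessments should instead be reported as unblinded.

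The cost is one corrected passage of text and one task reassigned among existing staff; Data collection already refers to more than one assessing researcher.

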**Fig. 1 Fig1:**
[figure not shown]
Flowchart describing the search strategy

### Interventions

The intervention for the EG will consist of an 8-week individual training regime (1-h individual training, three times per week). Sessions will be led by a physiotherapist specializing in PD and motor and cognitive exercise programs. This health professional will ensure adaptation, specificity, progression, variation, and safety of the training. Guidance for exercise in PD was underpinned by clinical experience and evidence from the European Physiotherapy Guidelines for PD [20]. Each session will start with a 10-min warm-up outside of the trampolines, comprising a variety of whole-body amplitude-based movements and walking activities. It will end with a 10-min cooldown incorporating breathing and low amplitude movements as active stretching. The sessions will consist of performing motor exercises on the trampolines while adding in motor and cognitive exercises that will progressively be increased. Motor exercises will include an array of frequently recommended movements for PD that directly enhance specific functional activities of daily living, such as multidirectional stepping in place, sitting and standing, standing with good posture under unexpected balance challenges, reaching in diverse directions (e.g., catching a ball), carrying soft objects (while standing and walking), walking, turning and running, and getting up from the floor/trampoline [20]. All these physical exercises will focus on reinforcing the use of high-amplitude, multidirectional movements with increasing speed and complexity. Because people with PD often depend on cues when performing motor tasks during the sessions, cueing strategies (cognitive, visual, tactile, or verbal) will be used according to the patient’s needs to promote good-quality movement and reduce compensations [20, 27, 28]. Cognitive exercises will target the 4 main cognitive domains particularly affected by PD: attention, working memory, executive function, and visual exploration [29]. The dual cognitive tasks will include standing, sitting/standing, stepping, or walking while performing cognitive tasks such as simple talking, memorizing lists of words, alternating sentences, spelling words backward, counting a 7-digit number forward/backward, and quick decision-making.

In Fig. 2, we can see a summary of the progression of activities without a very restrictive protocol to assure its specificity to the patient and also to better transfer to clinical practice. During the sessions, the therapist is required to modify the exercises for the patient and may include adjustments to the type of physical activities, length, use of verbal feedback, time for learning, and number and type of cognitive exercises added. Feedback from each session will be used to adapt the program to the personal needs of each participant. The proposed protocol is not restrictive, aiming to be highly focused on the individual dosage and specificity, which ultimately better represents and has a real impact on clinical practice.

**Fig. 2 Fig2:**
[figure not shown]
Lisbon Intensive Falls Trampoline Training (LIFTT) Program weekly progression

Additionally, safe fall landing strategies will be taught and reinforced throughout the program but specifically trained in the last two weeks. There is emerging evidence to suggest that these landing strategies can be safe and effective for a geriatric population [30]; however, this intervention has not been examined in a clinical physical therapy practice setting in PD. This will be an additional novelty of our program.

At the end of each session, the therapist will document in the study log any adverse event, patient feedback about the exercises and need for support, motives for absence, and any reported falls that occurred during the training.

To ensure participant retention, we facilitate traveling with reimbursement of costs and a list of concierge services to choose from. The team applying the intervention will be asked to express appreciation weekly, do follow-up calls when someone is absent, and share weekly results reached.

In the control group, participants will continue to receive their usual care from the health services and only receive the assessments. The intervention group will go back to usual care during follow-up.

### Data collection

Assessments will take place at APDPk by a blinded researcher in the week before (T0), after 8 weeks of training protocol (T1), and 3 months after the end of the program (T2). The same protocol will be applied, composed of scales/questionnaires and validated assessment instruments, referenced below. The researchers who will perform these assessments will not participate in the intervention. All participants will be assessed in the ON medication phase with the following specific clinical scales and tests that will have their order randomized. Patients will be assessed for (a) balance (Mini-BEST Test) [12], (b) gait (Motor and Cognitive Timed Up Go (TUG)) [12], (c) clinical impairments (Movement Disorder Society Unified Parkinson Disease Rating Scale (MDS-UPDRS)) [31], (d) frequency and severity of falls (falls weekly registry) [12], (e) fear of falling (Falls Efficacy Scale (FES-I)) [32], (f) physical capacity (6-min walking distance test (6MWD)) [12], (g) cognition (Montreal Cognitive Assessment (MoCA)) [33], and (h) quality of life (PDQ-8) [34, 35]. Additional gait and balance assessments will be conducted using accelerometers placed on the ankles and standing on a force plate. Participants will be asked to walk on a treadmill for 10 min at their preferred walking speed. Moreover, their balance will be tested in both eyes opened and closed conditions. They will be asked to remain still for 2 min. Researchers that will conduct the assessments will be trained by a senior and experienced researcher. The database obtained will undergo a double check (two different researchers) to identify potential failures/errors.

### Data analysis

We will perform descriptive and inferential statistics of data collected at T0, T1, and T2, to identify the differences between the two groups (EG and CG) and to evaluate which of these groups will have better results as a function of time (from T0 to T1 and T2). Assessment of reliability and correlation analyses will also be conducted. We do not anticipate the possibility of performing subgroup analysis for this study. The protocol will not change during the entire interventional period of the study; therefore, no interim analysis will be performed, nor do we anticipate the need for stopping guidelines.

For achieving the objective mentioned above, we will use a factorial (two-way) repeated measures (RM) ANOVA, considering a between-subject factor (treatment: EG, CG) and a repeated measures factor (time: T0, T1, T2). The two-way RM ANOVA will allow to evaluate the individual contribution of each factor and their interaction throughout time. The latent growth modeling (LMG) technique will be conducted to establish the effectiveness of the individual intervention on the growth of primary outcomes during the period between the beginning (T0) and the end (T2) of the program.

Regardless of the potential dropouts missing data, we will include all the participants in the statistical analysis (i.e., intention-to-treat analysis).

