# Lisbon Intensive Falls Trampoline Training (LIFTT) Program for people with Parkinson’s for balance, gait, and falls: study protocol for a randomized controlled trial

**DOI:** 10.1186/s13063-023-07131-4

**Published:** 2023-02-08

**Keywords:** Falls, Trampoline training, Effectiveness, Balance, Parkinson’s disease, Randomized controlled trial

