## Abstract

**Background:**

Falling and gait difficulties in people with Parkinson’s disease (PD) are associated with impaired reactive postural adjustments and impairments in attentional resources. Combined intensive balance motor and cognitive exercise can be beneficial. However, uncertainties persist regarding the true effects and safety when applying such training. Using trampoline beds may be a favorable safe environment for a highly intensive, cognitive, and balancing training approach. The primary goal of this randomized controlled trial is to assess the effects of an intensive cognitive-motor training program in a safe trampoline environment in addition to usual care on balance impairment, gait, physical capacity, fear of falling, falls frequency and severity, cognition, and clinical impairments in people with mild or moderate PD.

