**Methods:**

Sixty participants diagnosed with idiopathic PD, in stage 2–4 Hoehn and Yahr, with a clinical history of gait deficits and a fall history (at least one fall in the last 6 months) will be recruited and randomly allocated to an intervention group receiving cognitive-motor trampoline training or a control group undergoing their usual care. The intervention will consist of 8-week individual training sessions (1-h training, 3 days per week) led by specialized physiotherapists that will provide progressive, challenging training, and guarantee safety. Assessment will be conducted prior to and immediately after the 8-week intervention and at 3 months follow-up after participating in the study. Primary outcome measures will be balance performance (assessed using the Mini-BEST Test and nonlinear analysis) and change in gait parameters (Motor and Cognitive Timed-Up-Go and nonlinear analysis). Secondary outcomes will be change in clinical improvement (Movement Disorder Society Unified Parkinson’s Disease Rating Scale), falls (falls weekly registry), fear of falling (assessed using the Falls Efficacy Scale), physical capacity (6-min walk test), and cognition (Montreal Cognitive Assessment).

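### Falls from the weekly registry are left to a repeated-measures ANOVA that has no term for observation time and no count distribution

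*Protocol article*

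**What the plan says.** The Data collection section lists "frequency and severity of falls (falls weekly registry" among the measures assessed in the week before the programme (T0), after its 8 weeks (T1) and 3 months after it ends (T2).

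The Data analysis section opens with its scope: "We will perform descriptive and inferential statistics of data collected at T0, T1, and T2". It then names the model: "For achieving the objective mentioned above, we will use a factorial (two-way) repeated measures (RM) ANOVA". Its two factors, group and visit, cover both arms and all three assessments. No outcome is excepted. The only other model, latent growth modelling, is restricted: it is "on the growth of primary outcomes during the period between the beginning (T0) and the end (T2) of the program".

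Falls are not a primary outcome. The abstract says: "Secondary outcomes will be change in clinical improvement (Movement Disorder Society Unified Parkinson’s Disease Rating Scale), falls (falls weekly registry". They are nevertheless prominent. The title presents the programme "for balance, gait, and falls: study protocol for a randomized controlled trial", and the stated goal in the abstract covers "falls frequency and severity, cognition, and clinical impairments in people with mild or moderate PD".

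The article gives no count model, rate, exposure term, transformation or rank-based alternative for falls. It does not say how the weekly entries become a T0, T1 or T2 value.

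**The concern.** A Mini-BESTest score is a state measured at a visit. A fall count is a total over a period, and its size depends on how long that period is. Repeated-measures ANOVA treats the three values as the same quantity measured three times with normal errors of comparable variance. It cannot know that one value covers 8 weeks and another about 13.

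Three things are at stake:

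- The section asks which group does better as a function of time. With period totals, the time effect and part of the interaction reflect period length.
- With about 26 completers per arm and skewed counts, a few frequent fallers weigh heavily on the means.
- The output is a difference in mean counts, not a rate ratio, so it is hard to interpret or to compare across periods.

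**Working it through.** **Inputs from the article.** Two arms, 1:1; 26 per group needed before dropout (Sample size calculation). Period to T1 about 8 weeks; T1 to T2 3 months, about 13 weeks (Data collection). Allocation follows the T0 assessment (Randomization and blinding). The article states no fall rate, dispersion or power for falls, so there is no figure of its own to reproduce.

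**Assumptions.** Fall rate 0.1 to 0.5 per week, negative binomial dispersion k of 1 to 2, true rate ratio 0.5, and a T0 falls window of 1, 8 or 26 weeks.

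**1. Period totals.** Expected count = rate × weeks.
- Control, 0.25 per week: 0.25 × 8 = 2.0 to T1; 0.25 × 13 = 3.25 from T1 to T2. The ratio is 13/8 = 1.625, a rise of about 63% with no change in risk. It does not depend on the assumed rate.
- Trampoline group at rate ratio 0.5: 1.0 and 1.625.
- Group difference: 1.0, then 1.625. The effect is constant but appears to grow.
- The expected group difference at T0 is zero, because allocation comes afterwards.

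**2. Falls per week.** The group difference is 0.25 − 0.125 = 0.125 in both periods, so the artefact disappears. The variance of a weekly rate over w weeks is rate/w + k × rate². For rate 0.25 and k = 1:
- 8 weeks: 0.0313 + 0.0625 = 0.094
- 13 weeks: 0.0192 + 0.0625 = 0.082
- 1 week, if that were the T0 window: 0.25 + 0.0625 = 0.313

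**3. Skewness.** For mean m, skewness = (1 + 2km)/√(m(1 + km)). At m = 2: 5/√6 = 2.0 for k = 1 and 9/√10 = 2.8 for k = 2. Dividing by weeks does not change it. In simulation, with both arms pooled at rate ratio 0.5, it was about 2.4 to 3.4.

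**4. Simulation, 26 per arm.** The group-by-time F test (4,000 runs per setting) was compared with a negative binomial Wald test on falls over both post-baseline periods, with a log-exposure offset and the baseline count as covariate (250 runs per setting). Power at rate ratio 0.5, as the range over the assumed rates and dispersions:

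| T0 falls window | ANOVA, totals | ANOVA, per week | Negative binomial |
|---|---|---|---|
| 1 week | 27–68% | 11–29% | 40–72% |
| 8 weeks | 31–92% | 22–78% | 49–97% |
| 26 weeks | 12–22% | 31–93% | 56–96% |

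Rejection under no effect was 4.4–7.8% (totals), 4.2–7.0% (per week) and 3.6–9.6% (negative binomial). Sphericity failed: mean epsilon was 0.57–0.90 for totals and 0.65–0.92 per week.

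**5. Size-controlled repeat.** The Wald test is somewhat liberal, so part of its advantage in the table is not real. With a permutation p-value for the count test, the gain stayed large against totals with a 26-week baseline (13–16% versus 56–90%). It was clear in most settings against falls per week, and absent in some settings with totals and a 1- or 8-week baseline. ANOVA size was about 4–9% in these runs.

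**The case against.** The strongest reply is that the article never says raw totals are used. Frequency from a weekly registry can be read as falls per week, which removes the 8-versus-13-week problem, and the reduction to an analysis variable may be set out in a full protocol or analysis plan not shown. This stands in part: the period-length artefact is conditional on totals. It does not remove the point. The article does state the method, does not except falls, and on either scaling the model ignores the count distribution and the amount of observation behind each value.

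It is also true that both arms share the same windows, that the interaction test keeps roughly its nominal size, and that the power gain is not assured. At one setting (mean 3 falls, k = 2, rate ratio 0.4, 26 per arm), a size-controlled negative binomial test had 48.7% power against 47.4% for a plain t-test on counts. That t-test is not the planned ANOVA, but the result is a warning against quoting one power figure.

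A reader might infer more than the article supports:

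- *A false effect growing from T0 onwards.* Allocation follows T0, so a step from zero to a difference at T1 is the treatment effect. Only the T1-to-T2 step can be an artefact.
- *A one-week baseline count of falls.* The article places the T0 assessment in the week before the programme but gives no look-back for falls. The 6-month history in the abstract is an eligibility threshold.
- *Early leavers counted as low fallers.* Ethics and dissemination says those who stop the intervention continue to be followed unless they withdraw consent, and a classical repeated-measures ANOVA drops incomplete cases rather than scoring them low.

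**Conclusion.** The point holds as a mismatch between a stated method and one secondary outcome. On the article's own wording, falls go into a normal-theory repeated-measures ANOVA with no exposure term.

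With period totals, the mean rises about 63% from T1 to T2 at a constant fall rate, and a constant rate ratio shows as a difference growing by the same factor. That result needs only the visit schedule and the use of totals. With falls per week, skewness and unequal precision remain, and power is usually lower than with a count model. How much lower rests on the assumed rates, dispersion and baseline window. The simulated count model also pooled both post-baseline periods, so its power is not that of an analysis to T1 alone.

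The documents do not support a claim that the falls comparison would be falsely positive, since type I error for group-by-time is only modestly affected. The primary outcomes, balance and gait, are untouched. The change is worth making because falls are in the title and the stated goal, and the change is cheap.

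**What to change.** In Data analysis, except falls from the repeated-measures ANOVA and state:

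- Registry falls from randomisation to T1 are analysed with a negative binomial model with log(weeks observed) as offset. The same model to T2 is secondary.
- The model adjusts for baseline falls where a count is recorded. The article does not say that one is, so the baseline look-back should be defined; if no count exists, the covariate is omitted.
- The rate ratio is reported with its 95% CI. The p-value comes from a permutation test, because Wald tests are slightly liberal at this sample size.
- Falls during training sessions are tabulated separately. Therapists already log them (Interventions), and controls have no sessions.

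The offset also lets partial follow-up count in proportion to the weeks observed. The cost is a few sentences and slightly more programming. The follow-up data come from the registry already kept.
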